### Intervention

Autonomy-enhancing therapy’s goal is to enhance autonomy-connectedness at behavioral, attitudinal, and emotional levels by working on personal, autonomy-related goals.

The investigational treatment, autonomy-enhancing therapy, consists of 15 weekly 2-hour group sessions, following the existing autonomy-enhancing therapy protocol [21]. The autonomy-enhancing therapy protocol prescribes a mindfulness exercise, space to share progress toward personal autonomy goals, and the appointment of a chairperson for each session who, with therapist support, keeps time. Each week features different autonomy-related themes (eg, relationships, boundaries, body and sexuality, and emotions), including psychoeducation, exercises, homework, and discussion of autonomy-related difficulties. Autonomy-enhancing therapy groups typically consist of 8 participants (range 4‐10).

The autonomy-enhancing therapy protocol has been slightly adjusted to fit the existing structure of the last phase of treatment in the Center for Eating Disorders, GGZ Oost-Brabant, Helmond. In this phase of treatment, participants are part of a group that follows several treatment modules together. Relapse prevention is covered in standard treatment, so introductory, relapse prevention, and midpoint evaluation sessions are omitted, leaving 12 sessions. Additionally, new members continuously join the group in the last phase of treatment, so patients start with whatever theme is planned for that week, ensuring that all themes are covered, even if the starting point varies. In the last phase of treatment, patients participate for a minimum 3 to maximum 6 months, with continuation decided after an evaluation at 3 months. Continuation or discharge is determined by main practitioners, guided by input from the treatment team. Participation in the intervention stops when individuals are discharged. After finishing their ED treatment, many patients proceed to other forms of treatment (eg, trauma treatment, treatment focused on personality disorders, or general psychological support).

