### Analyses

Sample size and statistical power were approximated using G*Power (version 3.1.9.4). To detect a medium effect size (*f*^2^=0.15) in a regression with 7 predictors, 89 independent observations are needed for a power of 0.95 at α=.05. For the SCED analysis, with an intraclass correlation coefficient of 0.2, each participant’s 20 observations yield 4.17 independent observations [45], necessitating at least 22 participants. To ensure robustness, we aim for 30 participants (125 independent observations), achieving a power of 0.99. Considering a 20% dropout rate, we plan to recruit 36 participants. For the RM analysis, assuming 3 observations per participant, we obtain 30×2.14=64 independent observations, resulting in a power of 0.67 to detect a medium effect size (using α=.01).

Differences between individuals in their SCED data will be examined using visual analyses, presenting separate plots for all participants’ measures [46]. Visual analysis will evaluate changes in level, trend, variability, immediacy of effect, overlap between phases, and consistency across participants. Interview data will be used descriptively to better understand participants’ experiences of the intervention and their interpretation of change. The interview data will be reviewed and summarized to identify recurring experiences, perceived benefits and challenges, and considerations relevant to feasibility and future implementation.

The SCED data will be analyzed using a mixed model with 2 treatment periods, incorporating 2 dummy variables (treatment period 1 and treatment period 2, with baseline as the reference). A linear effect of time, centered within each period, represents the average change across periods. A random intercept and an autoregressive error structure will model the covariance structure. The primary hypothesis of the average decrease in ED symptoms is tested with 1 dummy for treatment period (1=treatment period 1 or 2, 0=baseline). This hypothesis will be tested for autonomy-connectedness.

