The RM data for all outcome variables will be analyzed using mixed models. Measurement will be modeled with 3 dummy variables (after treatment period 1, after treatment period 2, and after 3 months, all with baseline as the reference category), and an unstructured covariance matrix will model the random effects. The analyses will focus on the effect of dummy “post,” testing the hypothesis that scores improve compared with baseline. Mediation by autonomy-connectedness will be tested in two steps: (1) adding autonomy-connectedness to the model and (2) conducting a dependent-samples *t* test (1-tailed) comparing autonomy-connectedness after treatment and at the 3-month follow-up with baseline. Mediation will be concluded if (1) autonomy-connectedness affects the outcome variable in the mixed model analysis and (2) autonomy-connectedness improves over time in the *t* test, indicating a joint-significance test of mediation [47].

All analyses will control for ED diagnosis (dummy AN, with BN as the reference category). We will explore whether the development over time of ED, autonomy-connectedness, and the other outcome variables differ between the two EDs.

Hypotheses on change will be tested 1-tailed, with a significance level of .05 for the multiple baseline data and .01 for the RM data to correct for multiple testing. Missing values on the outcome variable do not affect mixed model analyses [45], whereas participants with missing autonomy-connectedness values will be excluded from the mediation analyses.

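### Missing data: an unconditional claim about mixed models needs its missing-at-random condition, and the mediation rule drops participants where dropping occasions would do

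*Protocol article*

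**What the plan says.** One sentence at the end of the Analyses section sets the missing-data rule. Its first half, supported by a citation, reads "Missing values on the outcome variable do not affect mixed model analyses". Its second half, introduced as a contrast, says that "participants with missing autonomy-connectedness values will be excluded from the mediation analyses".

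The same section defines the mediation test in two steps. Autonomy-connectedness is first added to the repeated-measures (RM) mixed model. A one-tailed paired t test then compares autonomy-connectedness after treatment, and at the 3-month follow-up, with baseline. Mediation is concluded if both steps succeed.

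The section also states that RM data for all outcome variables are analysed with mixed models. Autonomy-connectedness is one of those outcomes: Design and Secondary Outcome Measures list it among the 3-monthly questionnaires.

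On the course of treatment, the Intervention section gives a stay of 3 to 6 months and says "Participation in the intervention stops when individuals are discharged". The RM model nevertheless has a separate measurement after treatment period 2.

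**The concern.** The first half turns a conditional property into an unconditional one. A likelihood-based mixed model does not need complete records, but its estimates are protected only when missingness depends on observed data and the model is correct. Missing values also always cost information. The article itself plans for 20% dropout and foresees adherence difficulty with weekly forms, so the condition matters here.

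The second half fixes the unit of exclusion at the person. Because the 3-monthly questionnaires are filled in as one set, a missed session will usually lose outcome and mediator together. Deleting that occasion then costs little more than is already lost. Deleting the person also discards the other occasions, on which both were observed. Mediation is the third hypothesis, and the stated RM power is already modest.

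The rule also leaves the plan with two estimates of the same change. Autonomy-connectedness as an RM outcome is modelled on all observed values, while in the mediation test its change comes from complete pairs only. The two can disagree simply because the samples differ.

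**Working it through.** **Inputs from the Analyses section:** 30 participants; 3 RM observations each; intraclass correlation 0.2; f² = 0.15; 7 predictors; RM level .01; stated RM power 0.67.
**Assumed, not in the document:** the fraction q of RM occasions with autonomy-connectedness missing, taken as 5%, 10% and 20%; independence of missingness over occasions within a person; any one missing value triggers exclusion.

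**1. The plan's own figure.** Effective observations per person = m/(1 + (m − 1) × ICC) = 3/(1 + 2 × 0.2) = 2.14, and 30 × 2.14 = 64. For one coefficient, with noncentral t, df = 64 − 7 − 1 = 56 and noncentrality √(0.15 × 64) = 3.10, two-sided power at .01 is 0.67. The figure reproduces. (One-tailed, as the hypotheses are to be tested, it would be 0.76; I keep the stated basis below.)

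**2. Participants kept under person-level exclusion.** Kept = 30 × (1 − q)³. Person-occasions used are 90 × (1 − q)³, against 90 × (1 − q) if only the missing occasions are dropped.

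| q | participants kept | person-occasions, person-level | person-occasions, occasion-level |
|---|---|---|---|
| 5% | 30 × 0.857 = 25.7 | 77.2 | 85.5 (95%) |
| 10% | 30 × 0.729 = 21.9 | 65.6 | 81 (90%) |
| 20% | 30 × 0.512 = 15.4 | 46.1 | 72 (80%) |

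**3. What that means on the plan's power scale.** Under person-level exclusion the effective observations are participants kept × 2.14: 55.1, 46.9 and 32.9, giving power 0.58, 0.49 and 0.31. Under occasion-level deletion I average m/(1 + (m − 1) × 0.2) over the binomial number m of occasions observed. For q = 20% this is 0.512 × 2.143 + 0.384 × 1.667 + 0.096 × 1 = 1.833 per person, or 55.0 in all. The three rates give 62.1, 59.8 and 55.0, with power 0.65, 0.63 and 0.58. On this scale, person-level exclusion at 5% missing costs as much as occasion-level deletion at 20%. This is the plan's generic RM power, not a power calculation for the joint mediation test, which the article does not give.

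**4. Sensitivity to the assumptions.** If the same people miss everything, the loss is only q: 28.5, 27 and 24 of 30 remain. If the rule touches only the paired t test, one baseline and one later score are needed: 30 × (1 − q)² = 27.1, 24.3 and 19.2 pairs.

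**5. Whether missing outcomes can affect the mixed model.** A simulation used 3 visits, unstructured covariance, n = 30, a true change of −0.50 SD and about 20% missing at the last visit. Bias of the maximum-likelihood estimate was about 0 when values were missing completely at random or at random. With worse last-visit scores more often missing (assumed logit slope 1.5 per SD), bias was −0.21 SD at ICC 0.2 and −0.17 SD at ICC 0.5. This shows that the statement is conditional. It does not predict the bias in this trial, and it does not represent the weekly primary analysis.

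**The case against.** The sentence can be read as a practical contrast: a missing outcome does not force a case out of a mixed model, whereas a missing predictor does. On that reading the first half is shorthand, and the second half is a choice, not an error of fact. Complete-case analysis is inefficient and may be biased, but it is not biased under every mechanism. This stands, and it is why the point is about a missing condition and a poor choice of unit, not about two errors.

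The text also does not say whether one missing value is enough to exclude a person, and the missing rates and independence are mine. That stands too; the figures are a range under a literal reading.

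Two stronger readings are tempting and should not be drawn.
- A reader might infer that dropout will exaggerate improvement. The article does not say that worsening patients stop responding. Its Discussion ties the adherence worry to the repeated weekly measures, and frequent scores make missing at random more plausible because deterioration can be recorded before a patient stops.
- A reader might infer that everyone discharged at 3 months would be excluded, leaving only extended patients in the mediation analysis. Early discharge is part of the design, an occasion that does not apply is not naturally a missing value, and the t test uses the after-treatment and follow-up scores, not specifically the second treatment period.

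Finally, a missing-not-at-random sensitivity analysis is commonly left to an analysis plan that is not shown, so its absence is no finding.

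**Conclusion.** The point holds in limited form. The statement about missing outcomes is wrong as written because it lacks its missing-at-random condition. The mediation rule, as worded, excludes people instead of occasions and so discards usable data in an analysis with little to spare: about 26 to 15 of 30 participants kept, against 95% to 80% of person-occasions under occasion-level deletion. Those figures rest on 5% to 20% missing per occasion, independence over 3 occasions, and exclusion for any missing value; clustering within persons makes the loss smaller. Neither the direction nor the size of any bias can be derived from the article. The change is worth making because it is nearly free, and the stated timetable has data collection running to February 2027.

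**What to change.** 1. Reword the first half to say that the mixed-model estimates are *valid if outcomes are missing at random given observed scores*.
2. In the mediation mixed model, drop only the person-occasions on which autonomy-connectedness is missing.
3. Replace the paired t test in the second mediation step with the contrasts from the RM mixed model already planned for autonomy-connectedness: after treatment versus baseline, and 3-month follow-up versus baseline. The change is then estimated once, on all observed values.
4. State that an RM occasion that does not apply because of discharge at 3 months is not a missing value.

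A simple missing-not-at-random sensitivity analysis would be a useful option, but it is not needed to settle this point.

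The cost is wording and a little more analysis work, with no new data. The mixed-model contrasts carry their own missing-at-random assumption, which item 1 makes visible, so the statement about missing data becomes slightly less favourable.

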## Results

Data collection started in March 2024. As of May 2026, 18 participants have completed the study, and 6 have been enrolled. An additional 7 participants have been recruited, whose participation will depend on their individual treatment paths. Data collection is projected to finish in February 2027; results are expected to be published in the second half of 2027.

## Discussion

This study addresses the need for better treatments for ED by testing the effectiveness of autonomy-enhancing therapy, a potentially useful addition to ED treatment. On the basis of previous research on autonomy-connectedness and autonomy-enhancing therapy in other clinical populations [12,23], we hypothesize that autonomy-enhancing therapy will contribute to reductions in ED symptoms and improvements in autonomy-connectedness, self-esteem, quality of life, depression, and anxiety. More specifically, we expect increases in self-awareness and the capacity for managing new situations, alongside decreases in sensitivity to others, to contribute to treatment success. If supported, the findings may provide further evidence for the role of autonomy-connectedness as an underlying vulnerability and maintenance factor in ED. Additionally, this study will provide information regarding the acceptability and feasibility of implementing autonomy-enhancing therapy within routine ED treatment, which will inform future effectiveness research and broader implementation.

This study builds on previous findings suggesting that autonomy-connectedness predicts recovery from ED treatment [12], and that disturbances in self-functioning and interpersonal functioning play an important role in ED psychopathology. Existing ED treatments primarily focus on symptom reduction, while difficulties related to identity, self-definition, autonomy, and interpersonal functioning may remain insufficiently addressed. Autonomy-enhancing therapy may therefore complement existing approaches by targeting these broader underlying processes.

A particular strength of this study is its practice-based design within a specialized ED treatment setting, enhancing ecological validity and clinical applicability. In addition, the SCED multiple baseline design enables insight into the treatment process, as opposed to the “black box” effect of a randomized controlled trial.

Several limitations should also be considered. First, participants will continue to receive TAU alongside autonomy-enhancing therapy, making it difficult to determine whether observed changes can be uniquely attributed to autonomy-enhancing therapy. However, because autonomy-enhancing therapy is intended as an adjunctive intervention integrated into routine clinical care, studying it within the context of ongoing treatment may also increase the clinical relevance of the findings. Second, the relatively small sample size may limit generalizability. Third, highest relapse risk is reported to occur approximately 4 to 6 months after treatment, whereas the current study includes a follow-up assessment at 3 months after treatment due to feasibility constraints. This study may therefore not fully capture relapse during the period of highest risk. Finally, recruitment and adherence may prove challenging due to the repeated weekly measures.

Future research should further examine the effectiveness of autonomy-enhancing therapy in larger and more diverse ED populations, investigate long-term outcomes, and examine effects on relapse. If the present study yields promising findings, future studies could include larger controlled trials to further evaluate efficacy.

The findings of this study will be disseminated through peer-reviewed publications and presentations at scientific conferences, as well as at practice-oriented conferences for clinicians working in ED treatment. In doing so, we aim to contribute to the development of more comprehensive and relapse-sensitive approaches to ED treatment.
